### Two-stage analysis with random effects models

The two-stage analysis method [100] will allow us to overcome the problem of the availability of different study covariates. The pooled-estimates of the association of *MC1R* variants with each skin cancer type and each phenotypic characteristic will be calculated as follows.

First, study-specific ORs will be calculated by applying logistic regression to the data from each study to estimate the odds of skin cancer conditional on the presence of a *MC1R* variant (*X*), controlling for confounders *Z*_*k*_. For study *k* (*k = 1,…,K*), assuming just one confounder, the model is written as:

(4)$$\text{logit}(\pi_{\mathrm{ik}}/X)=\alpha_{k}+\beta_{k}X_{\mathrm{ik}}+\gamma_{k}Z_{\mathrm{ik}}$$

where *π*_*ik*_ is the conditional probability of skin cancer for subject *i* (*i = 1,…,n*_*k*_) of study *k*. Although *MC1R* variants were uniformly defined across studies, the confounders *Z*_*k*_ may be specific to a particular study. Analyses with original covariates and with recoded data will be performed and compared. The exposure log-odds ratio for study *k* is denoted *β*_*k*_, the confounding log-odds ratio is denoted *γ*_*k*_, and the *α*_*k*_ are the study-specific intercepts. The *β*_*k*_ are assumed to vary across studies according to the second-stage model:

(5)$$\beta_{k}=\beta +b_{k}+e_{k}$$

where *β* is the pooled-exposure log-odds ratio, *b*_*k*_ are random effects with *b*_k_ ~ N(0, *σ*^*2*^_*b*_), where *σ*^*2*^_*b*_ represents the variability of the study-specific exposure effects *β*_*k*_ about the population mean *β,* and *e*_*k*_ are independent errors with *e*_k_ ~ N(0, *σ*^*2*^_*k*_), where *σ*^*2*^_*k*_ describes the within-study variation of the *β*_*k*_. In the first stage ${\hat{\beta }}_{k}$and its variance ${\hat{\sigma }}_{k}^{2}$ are estimated from equation 4, separately for each study.

The two-stage estimator of the pooled exposure effect *β* is a weighted average of the ${\hat{\beta }}_{k}$, weighted by the inverse marginal variances of the ${\hat{\beta }}_{k}$, denoted $w_{k}={\left({\hat{\sigma }}_{k}^{2}+\sigma_{b}{}^{2}\right)}^{-1}$. Thus:

(6)$$\hat{\beta }=(\sum_{k}w_{k}{\hat{\beta }}_{k})/\sum_{k}w_{k}$$

(7)$$\mathrm{var}(\hat{\beta })={\left(\sum_{k}w_{k}\right)}^{-1}$$

Two methods [100] are frequently used to estimate the random effects variance *σ*^*2*^_*b*_ in equations 6 and 7. These methods are pseudo-maximum likelihood and moment estimation.

### Investigation of heterogeneity among studies

Homogeneity among the study estimates will be measured by Q statistic and I-Square [101], the latter representing the percentage of total variation across studies that is attributable to heterogeneity rather than to chance. Meta-regression analysis will be performed to investigate heterogeneity among study estimates, by evaluating the role of methodological characteristics of the studies and the characteristics of study populations.

### Joint association of MC1R and phenotypic characteristics with skin cancer risk

Stratified analysis for the association of *MC1R* variants with each skin cancer type will be performed for different phenotypic characteristics. The hypothesis of homogeneity of ORs among strata will be verified using the Breslow-Day test [102].

In order to identify combinations of *MC1R* variants and phenotypic characteristics associated with each skin cancer type, we will perform logic regression, a recently proposed tree-based statistical method intended for binary predictors [103]. This approach is particularly useful for detecting subpopulations at high or low risk of disease, characterized by high-order interactions among covariates, and thus the methodology could be well applied to the study of complex diseases like cancer. First, we will dichotomize continuous and categorical variables by choosing appropriate thresholds and by creation of dummy variables. For phenotypic characteristics we will define dummy variables in order to 1) have as much differentiation as possible in hair and eye color, and 2) separate the extreme classes of skin type and common nevi count from intermediate classes, because it has been suggested [21] that in the meta- and pooled-analysis setting misclassification affects the intermediate classes of exposure more than the extreme ones. Let *X*_*1*_*, X*_*2*_*,…, X*_*p*_ be the binary predictors obtained by dichotomization, and let *Y* be the binary response variable (case/control status). The appropriate logic regression model can be written as:

(8)$$\text{logit}(Y=1|X_{1},X_{2},\ldots ,X_{n})=\alpha +\sum_{j=1}^{k}\beta_{j}L_{j}$$

where *L*_*j*_ is a Boolean expression of the predictors *X*_*i*_, such as $L_{j}=X_{4}^{C}\wedge (X_{5}\vee X_{1}\vee X_{3}^{C})$ with ∧=AND, ∨=OR and ${}^{C}=\text{NOT}$. Logic regression could be generally applied to any type of regression outcome as long as the proper scoring function is specified. For the logic regression model in equation 8, the goal is to find the Boolean expressions *L*_*j*_ that minimize the binomial deviance, with the parameters *β*_*j*_ and the Boolean expressions *L*_*j*_ estimated simultaneously. The output from logic regression is represented as a series of trees, one for each Boolean predictor *L*_*j*_, and the associated regression coefficient. An example of a logic tree that may be applied to our pooled analysis is shown in Figure 1. Using this representation it is possible to start from a logic tree and obtain any other logic tree by a finite number of operations such as growing of branches, pruning of branches, changing of predictors and/or operators.

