## The M-SKIP project: rationale and aims

Melanocortin-1-receptor (*MC1R*, MIM#155555) is one of the major genes that determine skin pigmentation and it has been reported to be associated with risk of melanoma [14], possibly through the determination of the tanning response of skin to UV radiation [15-17]. However the relationship between some *MC1R* variants and melanoma also in darkly-pigmented European populations suggests that *MC1R* signaling may have an additional role in skin carcinogenesis beyond the UV-filtering differences between dark and fair skin [18]. In previous meta-analyses [14,19,20] authors found evidence of a significant association between melanoma, red hair and fair skin and the five *MC1R* variants R151C, R160W, D294H, D84E and R142H, and suggested a possible role in melanoma development, via non-pigmentary pathways, for I155T and R163Q variants. However, the specific contribution of each *MC1R* variant to melanoma development via pigmentary and non-pigmentary pathways could not be evaluated in meta-analyses due to the lack of individually joint information on *MC1R* variants and phenotypic characteristics.

The aim of the M-SKIP project is therefore to perform a pooled-analysis of individual data on sporadic skin cancer cases and controls with information on *MC1R* variants, in order to: 1) assess the association of *MC1R* variants with melanoma, basal cell carcinoma (BCC) and squamous cell carcinoma (SCC); 2) assess the association between *MC1R* variants and phenotypic characteristics, including hair and eye color, skin color, skin type, common and atypical nevi, freckles, and solar lentigines; and 3) perform stratified analyses on *MC1R* variants and skin cancer by phenotypic characteristics, and evaluate *MC1R*-phenotype interaction in skin cancer risk.

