**DNA source**				
Blood	24 (62%)	4645 (60%)	2743 (87%)	13304 (89%)
Buccal cells	14 (36%)	3161 (40%)	408 (13%)	1326 (9%)
Tissue	1 (3%)	0	0	245 (2%)

*NMSC* = non melanoma skin cancer.

^a^ healthy subjects are blood donors, friends or relatives of cases.

^b^ individual or frequency.

^c^ includes RFLP, SNaPshot, allele discrimination assay.

We calculated that the minimum required sample size to find a statistically significant association between a *MC1R* variant and melanoma assuming a similar association to that observed in our previous meta-analysis [14] (Odds Ratio (OR) = 1.5) is around 7,500 cases and 7,500 controls for rare variants (1-2% allele frequency in controls), and 1,400 cases and 1,400 controls for common variants (8-10% allele frequency in controls), with 90% statistical power. Sample size for gene-environment interaction analysis was also calculated with the program POWER, version 3.0 [96]. Considering the study of a simple two-way interaction between an environmental factor and a rare *MC1R* variant, around 5,000 cases and 5,000 controls would be needed to observe a multiplicative interaction effect of 2.0, arising to 16,000 cases and 16,000 controls to observe a smaller multiplicative effect of 1.5, both with 90% statistical power. For common *MC1R* variants, the same gene-environment interaction effects of 2.0 and 1.5 could be observed with around 1,200 cases and 1,200 controls, and with around 3,500 cases and 3,500 controls, respectively. Our sample size therefore is appropriate for the purpose of the analysis, and large enough to allow stratified and interaction analyses, especially to find even small interaction effects with the most frequent variants, and larger interaction effects for less common variants.

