**Figure 1 F1:**
[figure not shown]
**Example of a logic tree representing the Boolean expression “*****more than 50 common naevi*****V [*****skin type IV*****Λ (*****MC1R R151C*****V*****brown hair*****)]”.**

The searching for the optimum combinations of *MC1R* variants and phenotypic characteristics mostly associated with skin cancer will be undertaken by a (stochastic) simulated annealing algorithm [104-106]. This algorithm has a good chance to find a model that has the best or close to best possible score but, in the presence of noise in the data, typically overfits data. In order to select the best model, application of a combination of cross-validation and randomization tests has been suggested [104,105].

In an explanatory setting, at risk gene-phenotype combinations will be identified among a very large number of possible combinations by logic regression-based methods recently proposed [106,107]. The skin cancer risk of the identified subpopulations will be estimated within the pooled-analysis context using the two-stage analysis previously described.

Structural equation models will be also applied to eventually clarify the independent and dependent role of *MC1R* variants on skin cancer by phenotypic characteristics.

Finally, the role of environmental exposure will be investigated by entering new covariates in the models, by subgroup analyses and by studying gene-environment and phenotype-environment interactions using traditional and new proposed methodologies [108].

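### Effect modification by phenotype is tested with the Breslow-Day test on unadjusted tables, which does not match the plan's two-stage model and leaves the role of study undefined

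*Protocol article*

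**What the plan says.** The third aim includes an evaluation of MC1R-"phenotype interaction in skin cancer risk" (protocol article, rationale and aims). The section on the joint association of MC1R and phenotype plans stratified analyses: those of MC1R "variants with each skin cancer type will be performed for different phenotypic characteristics". The next sentence names the test: "The hypothesis of homogeneity of ORs among strata will be verified using the Breslow-Day test". No other test of OR homogeneity across phenotype strata is named. The Q statistic and I-square in the heterogeneity section concern studies.

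The main ORs are handled differently. In the two-stage section, "First, study-specific ORs will be calculated by applying logistic regression to the data from each study", with that study's confounders, and the estimates are then pooled with a between-study variance (equations 4 to 7). The stated reason is that "The two-stage analysis method [100] will allow us to overcome the problem of the availability of different study covariates".

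The joint-association section also plans logic regression and structural equation models. It returns to the two-stage method for subpopulations that logic regression identifies. Its closing sentence on interactions lists "gene-environment and phenotype-environment interactions using traditional and new proposed methodologies", and so does not cover gene-phenotype interaction.

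**The concern.** The Breslow-Day test takes one 2x2 table (variant by case status) per stratum. It accepts neither covariates nor random effects, so it tests a different quantity from the one that equations 4 to 7 estimate. The text leaves two readings of how study enters, and each has a fault.

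- **Strata are phenotype levels only.** All studies are then added into each table. Study becomes a confounder, and case-only and control-only studies enter without an internal comparison.
- **Strata are phenotype by study.** The test then rejects whenever ORs differ for any reason across the tables, including the between-study variation that equation 5 expects.

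At stake is the third aim: a false interaction, a masked one, or a test result that disagrees with the stratum ORs printed beside it.

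**Working it through.** **No figure to reproduce for this test.** The article gives none. The nearest is the main-effect sample size at OR 1.5 and 90% power. Using p1 = OR·p0/(1 − p0 + OR·p0), two-sided alpha 0.05 (assumed), a continuity correction and mid-range frequencies of 1.5% and 9% taken as carrier prevalence, I obtain 7,428 and 1,384 per group, against about 7,500 and 1,400 stated. I therefore take OR 1.5 as the planning effect.

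**Inputs from the document.** Table 2, melanoma cases/controls:

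- Northern Europe 858/8,095 (ratio 0.11)
- Central Europe 977/2,398
- Southern Europe 2,747/2,263 (ratio 1.21)
- North America 2,480/1,484
- Australia 744/290

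Table 3: 11 case-only studies with 2,646 melanomas (2,646/7,806 = 34%), 6 control-only studies with 1,464 controls, and one cohort with 68 melanomas and 6,559 controls.

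**Assumptions.** Areas stand in for studies. Carrier and phenotype frequencies by area are mine. The phenotype itself has OR 2.0 with melanoma. The variant has OR 1.5 in every area and stratum, so there is no interaction.

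**Reading 1, collapsed tables.** The stratum OR is (Σ carrier cases × Σ non-carrier controls)/(Σ non-carrier cases × Σ carrier controls), summed over areas. Example: Northern plus Southern Europe, carriers 20% and 4%, phenotype 60% and 20%.

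- Carrier controls without the phenotype: 8,095×0.4×0.20 + 2,263×0.8×0.04 = 647.6 + 72.4 = 720.0. Non-carriers: 2,590.4 + 1,738.0 = 4,328.4.
- Cases are shared out by prevalence × OR. North: weights 0.12, 0.32, 0.36, 0.96 (absent carrier, absent non-carrier, present carrier, present non-carrier), sum 1.76. South: 0.048, 0.768, 0.024, 0.384, sum 1.224.
- Carrier cases without the phenotype: 858×0.12/1.76 + 2,747×0.048/1.224 = 58.5 + 107.7 = 166.2. Non-carriers: 156.0 + 1,723.6 = 1,879.6.
- OR without the phenotype: 166.2×4,328.4/(1,879.6×720.0) = 0.53. The same steps with the phenotype give 229.4×4,320.1/(1,329.8×989.5) = 0.75. Ratio 1.42, Breslow-Day 8.37, p = 0.004.

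Rejection below is the chance that a noncentral chi-square (1 df, noncentrality equal to the Breslow-Day value on expected tables) exceeds 3.84. Areas are in the order North, Central, South, North America, Australia.

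| Carriers (%) | Phenotype (%) | OR absent / present | Ratio | Rejection |
|---|---|---|---|---|
| 20 everywhere | 60/50/20/40/50 | 1.50 / 1.50 | 1.00 | 5% |
| 12/10/8/10/12 | same | 1.31 / 1.33 | 1.01 | 5% |
| 15/10/5/10/14 | same | 1.05 / 1.12 | 1.06 | 11% |
| 20/12/4/12/18 | same | 0.91 / 1.01 | 1.11 | 25% |
| 20/12/4/12/18 | 10/5/1/5/8 | 0.95 / 1.12 | 1.17 | 22% |
| North and South only, 20/4 | 60/20 | 0.53 / 0.75 | 1.42 | 82% |

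With area kept as a stratifier (Mantel-Haenszel within each phenotype level), every row returns to 1.50 and 1.50. With carriers at 20/12/4/12/18 but the phenotype at 40% everywhere, both collapsed ORs are 0.97 and the ratio is 1.00. A false interaction therefore needs the phenotype mix to vary as well.

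**Dependence on one cohort.** If the cohort lies within one area, it must be Northern Europe, since no other area has more than 2,398 controls. Removing it leaves 858 − 68 = 790 cases and 8,095 − 6,559 = 1,536 controls. The two-area ORs then become 0.99 and 0.97 (ratio 0.98, p = 0.88). A second set of frequencies, with no phenotype effect, assumes 40% and 15% fair phenotype and carriers of 35/12% (fair/dark) in the North and 15/3% in the South. It gives collapsed ORs of 0.94 (fair) and 0.68 (dark), p about 0.007, with the cohort, and 1.18 and 1.10, p = 0.67, without it.

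**Reading 2, phenotype-by-area tables.** Carriers 20% everywhere, phenotype 60/50/20/40/50%, and ORs of 1.2, 1.5, 2.0, 1.5 and 1.3 by area, identical in both phenotype levels. Over ten tables Breslow-Day is 24.7 on 9 df, with rejection 96%. Within every area the ratio of ORs is exactly 1. Even Mantel-Haenszel ORs stratified by area differ here (1.68 absent, 1.47 present), because the phenotype mix weights the areas differently. A contrast formed within each area does not have this fault.

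**The case against.** The strongest reply is that the article never says that studies are collapsed. It prefers the two-stage method and describes the association of MC1R with each cancer type as estimated that way, and a journal article may leave the handling of study in a homogeneity test to the full plan. This stands: collapsing is an inference from strata defined by phenotype. It does not rescue the choice of test, which the article does name and which cannot carry covariates or random effects on either reading.

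A reader might also infer that stratum ORs will be reversed, as in the two-area examples. The documents do not support that. The test does not produce the reported ORs, and if these come from the two-stage model they are unaffected. The examples rest on assumed frequencies and largely on one cohort. They also need 8,095 + 2,263 = 10,358 controls with phenotype data, which in Table 1 only hair color (11,889) and eye color (10,720) reach. With all five areas the false interaction is none to modest.

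Finally, Breslow-Day is not the only analysis for the third aim. That is true, but equation 8 has a single intercept and no study term. Re-estimating risk in subpopulations found by logic regression does not test whether a variant's OR differs by phenotype.

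**Conclusion.** The point holds as a mismatch of method: the named test is unadjusted, does not correspond to the two-stage model, and is flawed whether study is collapsed or used as a stratifier. Under collapsing with a common OR of 1.5, the false ratio of ORs is about 1.0 to 1.2 with five areas (rejection 5% to 25%) and about 1.4 with Northern and Southern Europe alone. That last figure depends mainly on Northern Europe's case:control ratio of 0.11. With equal carrier frequencies there is no distortion. Under phenotype-by-study strata, moderate heterogeneity between areas alone gives 96% rejection in the example. All carrier and phenotype frequencies, the area ORs in that example and the use of areas for studies are assumptions. The documents do not establish that the stratum ORs themselves will be biased. This is a cheap improvement to a stated method.

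**What to change.** Replace the Breslow-Day test. In each study with cases, controls and the phenotype H, extend equation 4 with that study's own covariates:

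logit(π_ik) = α_k + β_k X_ik + δ_k H_ik + θ_k X_ik H_ik + γ_k Z_ik

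Pool the θ_k with equations 6 and 7, using weights 1/(var(θ_k) + σ²_θ), where σ²_θ is the between-study variance of the interaction. Report exp(θ), the ratio of ORs, with its 95% CI. The interval also shows how much heterogeneity the data leave open, whereas a non-significant test cannot verify homogeneity.

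Where cells are sparse, use a one-stage model stratified by study. This will arise: Table 1 has 1,088 controls with solar lentigines data, from at most six studies. An allele frequency of 1% to 2% (Hardy-Weinberg assumed, so 2.0% to 4.0% carriers) gives about 22 to 43 control carriers in all, or 4 to 7 per study if spread evenly over six.

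The cost is a little programming. Studies without the phenotype or a comparison group do not contribute; those without a comparison group give no within-study OR in the main two-stage analysis either. State also that the stratum-specific ORs come from the two-stage model, so that estimates and test agree.

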### Quality control, data coding and creation of the standardized dataset

We inspected the data for completeness and resolved inconsistencies with the investigator of each study. A number of subjects were excluded due to the following reasons: multiple-primary melanoma cases (N = 1596), missing data on *MC1R* variants (N = 1081), non-skin melanoma cases (N = 150), subjects with atypical mole syndrome and no skin cancer (N = 58), non first-primary melanoma cases (N = 24), familial melanoma cases, defined as subjects with two first-degree relatives or three or more any-degree relatives with melanoma (N = 25), other reasons including: unknown case/control status, duplicate subjects, or inappropriate controls (N = 232).

The following study-related variables were recoded uniformly: study country, study design, source of controls, application of case–control matching, methods to define phenotypic characteristics, genotyping methodology, whether genotyping was done in the same center for cases and controls and was blinded for case/control status, and DNA source. These variables were not used to assign a quality score to each study, but will be taken into account in meta-regression and sensitivity analyses. In addition, the variables listed in Table 1 were retrieved from each study if available, checked for quality, recoded in a standardized manner and entered in the main database. Finally, data on *MC1R* variants were entered for each subject. Quality controls and data coding were performed independently by two investigators, and inconsistencies were solved via consensus.

**Table 1 T1:** List of the main variables, number of original studies and related subjects per variable

**Variable**	**Studies (%) N = 39**	**Melanoma cases (%) n = 7806**	**NMSC cases (%) n = 3151**	**Controls (%) n = 14875**
Age	37 (95%)	7761 (99%)	3150 (100%)	14550 (98%)
Gender	39 (100%)	7801 (100%)	3151 (100%)	14853 (100%)
Ethnicity	38 (97%)	6770 (87%)	3142 (100%)	13833 (93%)
Body mass index	8 (21%)	557 (7%)	1380 (44%)	2226 (15%)
Smoking status	6 (15%)	2266 (29%)	419 (13%)	2286 (15%)
Intermittent sun exposure	21 (54%)	4493 (58%)	1266 (40%)	2286 (15%)
Continuous sun exposure	21 (54%)	4909 (62%)	741 (24%)	1938 (13%)
Sunburns	25 (64%)	4210 (54%)	1288 (41%)	2968 (20%)
Artificial UV exposure	16 (41%)	3842 (49%)	298 (9%)	1058 (7%)
Family history of skin cancer	27 (69%)	6660 (85%)	1289 (41%)	3318 (22%)
Family history of cancer other than skin	19 (49%)	4445 (57%)	371 (12%)	1630 (11%)

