**Source of controls**				
Hospital	6 (21%)	509 (10%)	1169 (37%)	1847 (12%)
Population or healthy^a^	21 (75%)	4651 (90%)	1982 (63%)	12872 (87%)
Mixed	1 (4%)	0	0	156 (1%)
**Case–control matching**^**b**^				
No	10 (45%)	3151 (61%)	1739 (55%)	9578 (71%)
Yes	12 (55%)	2009 (39%)	1412 (45%)	3833 (29%)

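### The logic regression search (equation 8) is written without age or sex terms, although both are almost completely recorded, so a phenotype could be selected because it tracks age or sex

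*Protocol article*

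**What the plan says.** The section on the joint association of MC1R and phenotypic characteristics states the purpose of the search: "In order to identify combinations of *MC1R* variants and phenotypic characteristics associated with each skin cancer type, we will perform logic regression". Equation 8 is introduced with "The appropriate logic regression model can be written as". Its right-hand side is an intercept plus a sum of coefficients times Boolean expressions, with no additive covariate. The selection criterion follows: "the goal is to find the Boolean expressions *L*_*j*_ that minimize the binomial deviance". The search over "phenotypic characteristics mostly associated with skin cancer will be undertaken by a (stochastic) simulated annealing algorithm" is followed by a reference to cross-validation and randomization tests for choosing the model. The risk of the subpopulations found is then estimated by the two-stage method.

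The neighbouring models are treated differently. The text after equation 3 says that covariates may be added to control confounding. Equation 4 carries a confounder term Z_k, which may differ by study; age and sex are not named there. In the joint-association section, new covariates are mentioned only for environmental exposure, after the search has been described.

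Table 1 shows how complete the two variables are: "Age 37 (95%) 7761 (99%) 3150 (100%) 14550 (98%)" and "Gender 39 (100%) 7801 (100%) 3151 (100%) 14853 (100%)". Table 3 gives the unmatched studies, in the order studies, melanoma cases, non-melanoma cases, controls: "No 10 (45%) 3151 (61%) 1739 (55%) 9578 (71%)".

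**The concern.** A tree search scored on an unadjusted deviance rewards any predictor whose frequency differs between cases and controls, whatever the reason. Suppose cases are older than controls and a trait becomes more or less common with age. The trait then lowers the deviance even if it carries no risk at a given age. The same holds for sex. Candidate phenotypes listed among the aims include common and atypical nevi, freckles and solar lentigines. That such traits vary with age is general subject knowledge and is not stated in the article.

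What is at stake is the selection. A trait that only marks age could enter a reported high-risk combination, or take the place of a real MC1R-phenotype combination. Cross-validation and randomization tests guard against fitting noise. An age-driven association is a real feature of the data and can pass both.

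The reason the article gives for avoiding a single covariate-adjusted dataset is that some covariates are missing in whole studies. That hardly applies to age and gender.

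**Working it through.** **1. Completeness of age and gender (Table 1).**

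| | Melanoma | NMSC | Controls | All |
|---|---|---|---|---|
| Age | 7761/7806 = 99.4% | 3150/3151 = 100.0% | 14550/14875 = 97.8% | 25461/25832 = 98.6% |
| Gender | 7801/7806 = 99.9% | 3151/3151 = 100% | 14853/14875 = 99.9% | 25805/25832 = 99.9% |

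These reproduce the rounded percentages printed in Table 1. Subjects without age: 25832 − 25461 = 371, or 1.4%. Two of the 39 studies have no age at all.

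**2. Matching (Table 3).** The matching rows cover 10 + 12 = 22 studies, which are the 21 case-control studies and the one cohort.

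- Melanoma cases in unmatched studies: 3151/(3151 + 2009) = 3151/5160 = 61%.
- Controls in unmatched studies: 9578/(9578 + 3833) = 9578/13411 = 71%.
- The cohort has 6559 controls, more than the 3833 in all matched studies, so it must be in the unmatched row.
- Without the cohort, 9 of 21 studies are unmatched. Controls: (9578 − 6559)/6852 = 3019/6852 = 44%. Melanoma cases: (3151 − 68)/(5160 − 68) = 3083/5092 = 61%.

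**3. Size of a spurious association.** Let a trait with no effect on disease have log-odds that change by s per year, and let mean age differ by d years between cases and controls. The crude OR is then roughly exp(s·d), somewhat closer to 1 in practice. Neither s nor d is in the article, so both are assumptions.

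| s | d | exp(s·d) | Simulated crude OR |
|---|---|---|---|
| −0.03 | 3 | 0.91 | 0.92 |
| −0.03 | 5 | 0.86 | 0.86 |
| −0.03 | 10 | 0.74 | 0.75 |
| +0.05 | 2 | 1.11 | about 1.1 |
| +0.05 | 5 | 1.28 | 1.25 |
| +0.05 | 10 | 1.65 | 1.56 |

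The +0.05 rows use an age SD of 15 years and the Table 1 counts for solar lentigines (1419 cases, 1088 controls) and common nevi (3817 and 1181), with 300 runs per setting. Tested singly at 5%, the null trait was significant in 4–5%, 21–25%, 80–92% and 100% of runs for gaps of 0, 2, 5 and 10 years. With age in the model the OR was 0.99–1.01 and 3–6% of runs were significant.

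**4. Effect on selection.** Two simulations scored every small Boolean term by binomial deviance, with 1,900 cases, 1,200 controls and 150 datasets per gap. Both included null traits with slopes of −0.03 and +0.03 per year. They differ in assumed prevalences and in the terms allowed: A scored one- and two-leaf terms, B two-leaf terms only. Simulation A also had a variant with OR 1.5 and a phenotype with OR 1.25. The table gives the share of runs whose best term contained an age-only trait.

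| Age gap | A, no age term | A, age added | B, no age term | B, age added |
|---|---|---|---|---|
| 3 years | 19% | 11% | 27% | 21% |
| 5 years | 39% | 18% | 48% | 27% |
| 10 years | 78% | 10% | 87% | 28% |

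With no gap the share was 9–11% in A and about 30% in B. With 150 runs, a share near 20% has a standard error of √(0.2 × 0.8/150) ≈ 3 percentage points. At 3 years the difference is therefore borderline in A and not visible against the no-gap level in B. At 5 and 10 years it is clear in both.

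**The case against.** The strongest reply is that equation 8 is the generic form of logic regression. The article prints simplified models throughout: equation 3 shows no covariate although covariates are then allowed, and equation 4 is shown with a single confounder. The full plan may adjust the search, and the text does not exclude age or sex from the dichotomized predictors. This stands in part: a reader might infer that the plan rules out adjustment, and it does not say so. But covariates are expressly provided for in the two other models and not here, and the stated purpose names only variants and phenotypes. A Boolean age leaf would have to win selection like any other leaf, so it would not adjust every scored model.

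Second, combinations found by the search are re-estimated within study with control for confounders, so one that only marks age should move towards an OR of 1. That is right if age and sex are in Z_k, which the article does not state. It does not change which combination was chosen or recover one that was displaced.

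Third, three stronger readings are tempting and are not supported:

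- That 71% of controls come from unmatched studies generally. One cohort drives this; the share is 44% without it. Unmatched also does not mean unbalanced in age.
- That matching is undone by pooling with case-only and control-only series. The article does not say these series enter the search. If they did, part of any age gap would lie between studies and overlap with the study effect, which is a separate matter.
- That the main product of aim 3 is compromised. Aim 3 is also served by stratified analyses with the Breslow-Day test, interaction analyses and structural equation models.

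**Conclusion.** The point holds for the logic regression discovery step. As written, the search criterion contains no age or sex adjustment, both variables are available for nearly everyone, and no later step corrects the selection itself.

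The size cannot be determined from the article, which gives no ages by case status and no relation of phenotype to age. If cases and controls have the same age and sex distribution, the effect is nil. Under the assumed slopes of ±0.03 per year, selection of age-only traits rises little at a gap of about 3 years and clearly at 5 to 10 years. A steeper assumed slope shows up at smaller gaps when a trait is tested singly. A reader might take the simulated shares as estimates for this database; they are illustrations under invented inputs, scored without the cross-validation and randomization steps.

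The change is worth making because it costs little and removes a known route to misleading selections. The article does not show that any selection is actually distorted.

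**What to change.** 1. Add age (in a flexible form, such as a spline or categories) and sex to equation 8 as fixed additive terms outside the Boolean trees, in every model scored by the search.
2. Use the same adjusted deviance in the cross-validation and randomization steps.
3. Name age and sex as members of Z_k when the selected combinations are re-estimated by the two-stage method.
4. Report age and sex by case status for the subjects who enter the search, so that readers can judge how much the adjustment matters.

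The cost is plan wording, a somewhat longer run time and the loss of subjects without age: 371 of 25,832 (1.4%) in the whole database. The two studies with no age would drop out of the adjusted search. The share lost among subjects with complete phenotypes cannot be worked out from Table 1.
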